### Control group

Participants in the control group receive standard prenatal care, including a leaflet about a healthy lifestyle in pregnancy, but no specific individual advice on diet, physical activity or weight gain in pregnancy is given. Data collection and distribution of questionnaires take place within routine prenatal care visits at the same time periods as in the intervention group.

### Study outcomes

#### Primary outcome

The primary outcome parameter is the proportion of participating women with excessive GWG as defined by the Institute of Medicine (IOM) [16].

#### Secondary outcomes

Secondary outcome parameters include:

– incidence of gestational diabetes (24^th^-28^th^ week of gestation, via an oral glucose tolerance test), glycosylated haemoglobin concentration (30^th^-34^th^ week of gestation),

– other pregnancy complications such as preeclampsia,

– anthropometric measures and health status of the newborns (birth weight, height, head circumference, LGA, small for gestational age (SGA), APGAR-Score, pH),

– obstetric complications (mode of delivery, induction of labour, rate of caesarean sections etc.),

– maternal dietary and physical activity habits during pregnancy and after delivery,

– maternal body weight after delivery (6-8 weeks postpartum),

– maternal mental health and post natal depression.

#### Follow-Up

It is planned to add a follow-up observation programme up to the age of 5 years. Follow-up parameters include breastfeeding and infant feeding practices, growth development and health status of the offspring (including weight and height measurement) as well as maternal weight development.

### Outcome measures and data collection

#### Weight measurements, documentation of pregnancy and obstetric complications

GWG is calculated as the difference between maternal weight at the last prenatal visit and weight at the first visit. The self-reported pre-pregnancy weight is documented at the time of recruitment. At every antenatal visit, weight, blood pressure, urine analysis data as well as pregnancy complications are routinely documented in the maternity card. A standard operation procedure is provided to the participating practices detailing weight measurement. In Germany, maternity cards are delivered to every pregnant woman at their first gynaecological visit as soon as pregnancy is confirmed. To retrieve data regarding complications during pregnancy and delivery and infant anthropometrics, practice staff will copy maternity cards and birth records at the first postnatal visit.

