## Background

The global prevalence of overweight and obesity has reached an epidemic dimension. In this context, the prevalence of overweight and obesity among women of reproductive age increased substantially [1,2]. Maternal overweight or obesity is associated with a variety of pregnancy and obstetric complications [3-7], such as gestational diabetes mellitus (GDM) [8], preeclampsia [9-11] and an increased risk for macrosomia [12] and caesarean delivery [13,14].

Likewise, recent data suggest that excessive GWG may result in a similar risk profile. Excessive GWG was found to be associated with an increased risk for many adverse maternal and fetal outcomes [15,16] such as large for gestational age (LGA) newborns [17-19] and long-term maternal weight retention after delivery [20-23]. Furthermore, GWG has been reported to be a significant risk factor for childhood obesity [24-33].

To support an optimal pregnancy outcome, the US Institute of Medicine (IOM) provided recommendations for GWG stratified according to BMI of the women before pregnancy [16]. Unfortunately, in many countries including the USA, but also in Germany, an increasing proportion of pregnant women exceed these recommended thresholds [16,25,34,35].

Growing evidence suggests that lifestyle during pregnancy and in the early postnatal period is considerably influencing fetal and infant growth and development. This is an important observation, as pregnancy and the early postnatal period represent critical stages of development for the offspring and may “programme” the risk of metabolic disorders later in life [36,37]. To interfere with this potentially vicious cycle [38,39], adequate intervention strategies which can be introduced into medical practice are urgently required. Some recent studies focussing on a healthy lifestyle during pregnancy and consisting of a balanced diet and regular physical activity showed a reduction in the risk of excessive GWG [40-43].

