### Study population

#### Inclusion criteria

Women aged 18 to 43 years with a singleton pregnancy, a pre-pregnancy BMI ≥ 18.5 kg/m^2^ and ≤ 40 kg/m^2^, and sufficient German language skills are eligible for the study. These pregnant women are recruited before the 12^th^ week of gestation and written informed consent is mandatory.

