**Figure 1 F1:**
[figure not shown]
Study scheme of the GeliS study.

*Visit 0* (≤ 12^th^ week of gestation) represents the screening examination. After checking inclusion and exclusion criteria and obtaining written informed consent, each participant obtains a folder containing questionnaires (on dietary habits and supplements/physical activity/maternal mental health) as well as a pedometer (Beurer GmbH, Ulm, Germany) with adequate instructions.

*Visit 1* (12^th^-16^th^ week of gestation): Detailed information about healthy diet and physical activity in pregnancy is given in a face-to-face session of 30 to 45 min. duration. The importance of a healthy lifestyle during pregnancy and its determining factors are explained. Pregnant women learn to handle the principles of healthy eating and to understand the risks of alcohol, smoking and foodborne infections during pregnancy. Further advice relates to GWG, weight monitoring and to critical nutrients in pregnancy (folic acid, iodine, and iron). A list of adequate prenatal physical exercise programmes, brochures including recommendations for a balanced diet in pregnancy as well as a chart for adequate weight gain according to baseline BMI category to self-monitor weight development are handed out. The questionnaires distributed in *Visit 0* are collected.

*Visit 2* (16^th^-20^th^ week of gestation, 4 weeks distance between the two visits): Specific and detailed individual counselling targeting dietary habits and physical activity also considering the information from the first set of questionnaires is given. Moreover, women are motivated to participate in a standardised two hour oral glucose tolerance test (OGTT) between the 24^th^ and 28^th^ week of gestation, and an appointment for the OGTT is fixed.

*Visit 3* (30^th^-34^th^ week of gestation): Repetition and consolidation of contents from the previous visits, with an emphasis on weight monitoring. Counsellors provide information on prenatal maternity courses, post natal exercise classes and on specific problems, such as water retention or back complaints. In addition, the importance of breastfeeding is addressed. A venous EDTA blood sample for measurement of glycosylated haemoglobin (HbA1c) is collected. The second set of questionnaires is handed out.

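### The primary outcome is labelled excessive GWG by the IOM, but gain is counted from an unnamed first visit, so both arms' proportions are understated and the contrast is moderately diluted

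*Protocol article*

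**What the plan says.** Under Primary outcome, the protocol article names the endpoint as "the proportion of participating women with excessive GWG as defined by the Institute of Medicine (IOM"). The Background describes the IOM guidance as "recommendations for GWG stratified according to BMI of the women before pregnancy". Eligibility under Inclusion criteria also uses pre-pregnancy BMI.

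The calculation is in the section on weight measurements and documentation of complications: "GWG is calculated as the difference between maternal weight at the last prenatal visit and weight at the first visit". The next sentence adds: "The self-reported pre-pregnancy weight is documented at the time of recruitment". That weight does not enter the formula. Nothing elsewhere in the article adapts the IOM limits to a later starting weight or adds back earlier gain.

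The starting visit is not named. Three readings are possible:

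- the first gynaecological visit, when the maternity card is issued (same section);
- Visit 0, described in the legend of Figure 1 as "≤ 12^th^ week of gestation) represents the screening examination";
- Visit 1, in weeks 12-16, the first counselling session.

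**The concern.** The limit a woman is judged against is indexed to her state before pregnancy, while the gain compared with it starts later. A woman whose total gain is just above her limit, part of it gained before the first visit, is counted as not excessive. A woman who lost weight early could be misclassified the other way, but where early change is a gain the rule undercounts.

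Two things are at stake. The trial's headline figure would carry the IOM label without being the IOM proportion. And because the starting visit is open, two analysts could obtain different primary results from the same data, in a trial that is not blinded.

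**Working it through.** **Inputs from the protocol (Power calculation; Study design and setting).** Control 40%, intervention 30%, power 90%, alpha 0.05, intraclass correlation 0.005, 1900 women needed, ten regions in five pairs.

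**Inputs assumed, because the article gives none.** The margin of a woman's gain over her limit is normal with SD 4-7 kg. Every woman has the same omitted early gain of 0.5, 1 or 2 kg. The 40% and 30% are taken to hold for gain counted from pre-pregnancy weight.

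**Step 1: reproduce the plan's 1900.**

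- Two-sided pooled formula: n per arm = (1.960 × √(2 × 0.35 × 0.65) + 1.282 × √(0.24 + 0.21))² / 0.10² = 477, or 496 with continuity correction.
- Cluster size: 1900/10 = 190. Design effect: 1 + 189 × 0.005 = 1.945.
- Total: 2 × 477 × 1.945 = 1856, or 2 × 496 × 1.945 = 1929.

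These bracket 1900 within 3%, so the sample size is not at fault. The effective size per arm is 950/1.945 = 488, which gives power 0.907 for 40% versus 30%.

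**Step 2: apply the first-visit rule.** With omitted gain g:

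- observed control rate = 1 − Φ(0.253 + g/SD)
- observed intervention rate = 1 − Φ(0.524 + g/SD)

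Example with SD 5 kg and g = 1 kg: 1 − Φ(0.453) = 32.5% and 1 − Φ(0.724) = 23.4%. The difference is 9.1 points and power at 1900 women is 0.886.

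| SD (kg) | Omitted gain (kg) | Control | Intervention | Difference (points) | Power at 1900 |
|---|---|---|---|---|---|
| 4 | 0.5 | 35.3% | 25.8% | 9.5 | 0.895 |
| 4 | 1 | 30.7% | 21.9% | 8.8 | 0.879 |
| 4 | 2 | 22.6% | 15.3% | 7.3 | 0.829 |
| 5 | 0.5 | 36.2% | 26.6% | 9.6 | 0.898 |
| 5 | 1 | 32.5% | 23.4% | 9.1 | 0.886 |
| 5 | 2 | 25.7% | 17.8% | 7.9 | 0.852 |
| 6 | 0.5 | 36.8% | 27.2% | 9.6 | 0.900 |
| 6 | 1 | 33.7% | 24.5% | 9.2 | 0.890 |
| 6 | 2 | 27.9% | 19.6% | 8.3 | 0.865 |
| 7 | 0.5 | 37.3% | 27.6% | 9.7 | 0.901 |
| 7 | 1 | 34.6% | 25.2% | 9.4 | 0.893 |
| 7 | 2 | 29.5% | 20.9% | 8.6 | 0.873 |

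**Step 3: share of truly excessive control women who are missed** (1 − observed rate/0.40). About 7-12% at 0.5 kg, 14-23% at 1 kg and 26-44% at 2 kg.

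The power figures use the plan's design effect and a normal approximation. They serve to compare scenarios, not to replace the plan's calculation.

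**The case against.** **A measured starting weight is defensible.** Practices receive a standard procedure for weighing, and self-reported weight has error. Because the trial is open and randomised by region, a woman may report her weight when allocation is already known. This stands, and it makes the choice of baseline partly a trade-off. But the protocol does not give this reason, does not adapt the limits, and depends on pre-pregnancy weight anyway for BMI category.

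**The omitted gain may be small.** Numbered study visits are capitalised, whereas the formula uses lower case in a paragraph about maternity-card records. The first antenatal visit is therefore the more natural reading, and the 2 kg rows lean on the least likely one. This also stands. A condensed article may leave the exact visit to the full protocol, so the missing name alone would not be a finding. The mismatch with the IOM label remains on any of the three readings.

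**The article does not state from which weight the IOM counts gain.** It states only that the limits are stratified by pre-pregnancy BMI. Counting from pre-pregnancy weight is the reading consistent with that, and the figures above assume it.

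Three stronger conclusions are tempting, and the documents do not support them:

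- *The fall of about 3-17 points in the control rate rivals the 10-point effect.* The fall is a change of level that lowers both arms together, while the 10 points is a difference between arms. The relevant comparison is 10 points against about 7-9.7.
- *The rule biases the comparison.* One rule covers all women, and under Control group the data collection periods match those of the intervention arm. If the arms differed by 0.5 kg in mean omitted gain, a spurious difference of about 2.7-4.7 points would follow from a 40% rate, but nothing in the documents suggests such a gap.
- *The 40% planning rate rests on whole-pregnancy gain and so does not match the endpoint.* The power section does not state the starting weight behind the register figure, so neither match nor mismatch can be shown.

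**Conclusion.** The point holds in a limited form. The formula does not match the definition it is meant to serve. Where early change is a gain, the reported proportion understates the IOM proportion in both arms and moderately dilutes the contrast.

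Under the assumptions stated, power stays at 0.83 or above throughout, and at about 0.88-0.90 if no more than 1 kg is omitted. The absolute proportions are affected more: the control rate could read anywhere from about 23% to 37% instead of 40%. The true size is unknown, because the documents give neither early gain nor an SD. The main consequence is for what the trial can claim about IOM-defined excess. Validity of the randomised comparison would be threatened only if the timing of the first weight differed by arm.

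**What to change.** Amend the outcome definition in one of two ways.

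1. **Preferred.** For the IOM classification, define GWG as the weight at the last prenatal visit minus the pre-pregnancy weight documented at recruitment. Pre-specify gain from the first measured weight as a sensitivity analysis.
2. **If a measured baseline is kept.** Name one early maternity-card weight, taken before Visit 1 and the same in both arms. State that the result is not the full-pregnancy IOM proportion. Pre-specify the classification from pre-pregnancy weight as a sensitivity analysis.

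Either way, report both versions, and fix the choice before outcome data are examined.

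The cost is a sentence or two in the definition and one further analysis. No new data are needed. The downside of the first option is reliance on self-report, with reporting error and possible knowledge of allocation when the weight is given. The sensitivity analysis is there to show whether this matters.

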#### Questionnaires

#### Screening-questionnaire

All women contacted are asked to complete a short anonymous questionnaire containing demographic and anamnestic data independent of study participation.

#### Dietary assessment

Dietary habits are recorded twice during pregnancy and once after delivery using a validated Food Frequency Questionnaire (FFQ) according to the DEGS-Study (“German Health Interview and Examination Survey for Adults” conducted by the Robert Koch Institute) [50]. Questions on the intake of dietary supplements are added. Women attending the intervention group receive questionnaires at *Visits 0*, *3* and *4*. Women in the control group receive FFQs at the same time points.

#### Physical activity assessment

Physical activity is assessed at three time points in both groups (analogous to FFQs) using the validated “Pregnancy physical activity questionnaire” (PPAQ), modestly adjusted to German habits [51]. In addition, a subgroup of women in the intervention group (n = 250) and in the control group (n = 250) are asked to carry a pedometer for seven consecutive days. Daily steps are documented in a personal diary which is handed out and completed at the same time points as the FFQ and the PPAQ.

#### Maternal mental health

In collaboration with the Mental Health Research Unit of the Helmholtz Zentrum München we have defined a questionnaire with validated elements (WHO-5; PHQ-4; questions from the KORA study - a research platform that is used by national and international research teams [52]). The mental health questionnaire is handed out and collected at the same time points as the FFQ and the PPAQ.

#### Post natal depression

Using the Edinburgh Postnatal Depression Scale (EPDS-Scale) postnatal depression is recorded at 6-8 weeks after delivery. The German version validated by Bergant et al. [53] will be used.

#### Evaluation

To assess the acceptance of the lifestyle programme, all participants in the intervention group obtain an evaluation form at the end of the intervention (*Visit 4*).

#### OGTT and HbA1c

To test for gestational diabetes mellitus (GDM), a standardised two-hour oral glucose tolerance test (OGTT) is offered to all participants between the 24^th^ and 28^th^ week of gestation. Tests are performed by the participating gynaecological practices according to the 2011 guidelines of the German Diabetes Society (DDG) and the German Society of Gynaecology and Obstetrics (DGGG) [54] which is in line with the guidelines of the International Association of the Diabetes and Pregnancy Study Groups (IADPSG) [55]. After an overnight fast, serum glucose level is measured before, one and two hours after intake of 75 grams glucose (Dextro®OGT, Roche, Mannheim). Treatment will be performed at the discretion of the participating gynaecologist. Every participating gynaecological practice will receive information about the DDG/DGGG guidelines for the management of gestational diabetes [54] and is asked to consider these principles as soon as GDM is diagnosed.

To obtain additional information on the presence and severity of diagnosed GDM, EDTA blood is collected for the measurement of the glycosylated haemoglobin concentration between the 30^th^ and 34^th^ week of gestation.

#### Follow-Up – well baby check-up booklet

Follow-up interviews (by phone call or e-mail, upon preference) will be arranged after one, and annually up to 5 years after delivery to record maternal body weight as well as infant anthropometrics. The infant anthropometrics are based on measured data from the well baby check-up booklet provided to all mothers in Germany at birth to promote regular health examinations by the family pediatricians. This is part of the free health check-up programme for infants in the German health care system. The (preschool-) programme comprises standardised health examinations at six time points during the first year of age (immediately after delivery, 3^th^-10^th^ day of age, 4^th^-5^th^ week of age, 3^th^-4^th^ month of age, 6^th^-7^th^ month of age, 10^th^-12^th^ month of age) as well as annually up to the age of five (21^th^-24^th^ month of age, 34^th^-36^th^ month of age, 46^th^-48^th^ month of age, 60^th^-64^th^ month of age). In Bavaria, the programme is currently utilized by approximately 84.5% of all parents [56]. All mothers are explicitly encouraged to participate in this programme. In addition, breastfeeding and infant feeding practices are assessed and documented. All data are pseudonymised before they are transferred to data management at the Münchner Studienzentrum for database entry.

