*Visit 4* (6^th^-8^th^ week postpartum): The fourth counselling session includes dietary advice during breastfeeding and information on infant feeding principles. Full breastfeeding is recommended at least up to the age of 4 months. If not returned yet, the second set of questionnaires is collected and the third set of questionnaires (dietary habits and intake of supplements/physical activity/post natal depression/evaluation) is handed out together with a free envelope to return the questionnaires. Maternal weight is measured and documented at each visit.

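### Maternal weight is measured at the practice up to 6–8 weeks postpartum but collected only by phone or e-mail in years 1–5, so method and time are confounded and reporting error may differ by arm

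*Protocol article*

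**What the plan says.** The protocol article describes three sources of maternal weight.

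- **Before pregnancy** (Weight measurements, documentation of pregnancy and obstetric complications): "The self-reported pre-pregnancy weight is documented at the time of recruitment".
- **Study visits up to Visit 4, 6–8 weeks postpartum** (Visit 4 description in the lifestyle intervention programme): "Maternal weight is measured and documented at each visit". The weight-measurement section adds that "A standard operation procedure is provided to the participating practices detailing weight measurement".
- **Years 1 to 5**: "Follow-up interviews (by phone call or e-mail, upon preference) will be arranged after one, and annually up to 5 years after delivery". The mother's weight and the infant's measurements are both collected at these contacts (section Follow-Up – well baby check-up booklet).

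For the child, the same section continues: "The infant anthropometrics are based on measured data from the well baby check-up booklet". It names no measured source for the mother.

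The Follow-Up section lists as parameters "growth development and health status of the offspring (including weight and height measurement) as well as maternal weight development". The abstract names maternal weight retention among the secondary outcomes, and the Secondary outcomes section lists maternal weight at 6–8 weeks after delivery. Study design and setting calls the trial open. Weight counselling and a self-monitoring chart go to the intervention arm; the Control group section says that controls receive no specific individual advice on weight gain.

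**The concern.** Reducing the risk of maternal obesity is one of the trial's stated aims, and after week 8 the remote interview is the only source of maternal weight that the article describes. Two difficulties follow.

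First, the last practice-measured value and the first remote value differ in both time and method. If reported weights are off by some average amount, that amount appears as weight change between 6–8 weeks and year 1, and nothing in the data can separate the two.

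Second, one arm has been taught to watch and chart weight, and participants know which programme they received. Intervention mothers might report more accurately because they weigh themselves more, or more favourably because they were given a weight goal. Either would make the reporting error depend on arm and would enter the long-term comparison as if it were an effect of the programme. The free choice between phone and e-mail adds a further source of variation that is not controlled.

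This is a matter of data collection, so an analysis plan cannot repair it afterwards: whether a reported weight was weighed or recalled is not recoverable unless it was asked at the time.

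**Working it through.** **Where an error goes.** Let *b*(arm) be the mean reporting error at a given follow-up year, with no mean error in practice weights.

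- Within an arm, observed change from 6–8 weeks to year 1 = true change + *b*(arm). Any non-zero *b* is confounded with time.
- Between arms in the same year, observed difference = true difference + [*b*(intervention) − *b*(control)]. A common error cancels; only a differential error remains.
- Retention against the self-reported pre-pregnancy weight subtracts a report made at recruitment, before counselling. That baseline cannot carry a reporting difference caused by the counselling, so subtracting it does not remove one that arises later.

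**The plan's own figures, as a check on the inputs.** The point disputes no stated number, but the illustration borrows the clustering inputs of the Power calculation section (40% v 30%, 90% power, alpha 0.05, intraclass correlation 0.005, ten regions).

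- Individually randomised, two-sided: 477 per arm, 954 in total (496 and 992 with continuity correction).
- Design effect at 1900/10 = 190 per region: 1 + 189 × 0.005 = 1.945.
- 954 × 1.945 ≈ 1856; 992 × 1.945 ≈ 1929. These bracket the stated 1900, at which power is 90.7%. The figure reproduces.
- 2500 less 25% drop-out until delivery: 2500 × 0.75 = 1875 women.

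**Illustration for an arm difference in mean weight change.** Assumptions that are not in the documents: SD of weight change 4–8 kg; differential reporting error 0.25–0.5 kg; no loss after delivery; the 0.005 intraclass correlation, set for a binary outcome, carried over to weight change.

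- Women per region: 1875/10 = 187.5. Design effect: 1 + 186.5 × 0.005 = 1.93.
- SE = SD × √(4/1875 × 1.93) = SD × 0.0642.
- Shift in SEs = differential error / SE.
- Chance of a nominally significant result when there is no true difference (normal approximation) = 1 − Φ(1.96 − shift) + Φ(−1.96 − shift).

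| SD (kg) | SE (kg) | 0.25 kg: shift; false rejection | 0.5 kg: shift; false rejection |
|---|---|---|---|
| 4 | 0.26 | 0.97 SE; about 16% | 1.95 SE; about 49% |
| 8 | 0.51 | 0.49 SE; about 8% | 0.97 SE; about 16% |

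The range is therefore about 0.5–1.9 SE. Loss to follow-up between delivery and year 5 would raise the SE and lower these ratios, as would a larger intraclass correlation. A t reference suited to ten regions would also lower the rejection rates.

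**The case against.** The strongest reply is that little of the harm is written into the plan.

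- **No joined trend.** A reader might infer that the plan runs the measured and reported weights together as one trajectory, or takes year 1–5 retention from a measured antenatal weight. No section does either. Maternal weight development is only listed as a parameter of a planned follow-up programme. This stands.
- **No known bias.** A reader might infer that the trajectory does shift downward at year 1 and that retention is biased low. The documents contain nothing on the size or direction of reporting error, so only the possibility is supported. This stands.
- **Common error cancels.** Both arms use the same method at each time, so a shared under-report leaves the same-year comparison unbiased. This stands, and it confines the threat to the comparison to differential error, for which the documents offer plausibility and no data.
- **Measured coverage is not complete.** Pre-pregnancy weight is self-reported, so the earlier series is not measured throughout. Weighing of controls at 6–8 weeks is implied by the shared timing of data collection rather than stated. Self-report in years 1–5 is likewise inferred from the contact mode.
- **A condensed article.** Interview wording and derivation of variables may sit in the full protocol. This stands in part. However, the article states the mode of contact and, in the next sentence, a measured source for the child only. The contrast is in the text and is not merely a silence.

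**Conclusion.** The point holds as a design weakness in a planned follow-up parameter that is cheap to reduce. The move from practice measurement to remote report is in the text. It confounds method with time between 6–8 weeks and year 1, and it leaves the year 1–5 arm comparison open to differential reporting in an open trial that coaches one arm on weight. The primary outcome and maternal weight at 6–8 weeks are not affected.

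The size is not known. The 0.5–1.9 SE range shows that a differential error of a few hundred grams could matter at this sample size. It rests wholly on the assumed SD, the assumed differential error, full retention after delivery and an intraclass correlation borrowed from another outcome. It should not be read as an estimate of bias in this trial.

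**What to change.** 1. At each annual contact, use one fixed request in both arms and both contact modes: weigh on a scale that day and report the reading.
2. Record whether the value was weighed or recalled, and whether it came by phone or e-mail. Tabulate both by arm.
3. Base the year 1–5 maternal result on the arm comparison within the same year. Add a sensitivity analysis restricted to weighed values. That restriction selects on something that happens after randomisation, so it supports the main comparison and does not replace it.
4. Label the year 1–5 weights as reported, and state that the change from 6–8 weeks to year 1 is not to be read as pure weight change.
5. Optionally, ask mothers in both arms for their weight just before they are weighed at Visit 4. This is a limited check on whether reporting differs by arm. It is not a full calibration: a woman about to be weighed may report differently from one answering remotely years later.

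The cost is a slightly longer annual interview, two data fields and one extra sensitivity analysis, with no added visits. A reading from a home scale is still a report from an unstandardised instrument, so the change narrows the problem without removing it. It has to be in place before the annual contacts begin, and item 5 before Visit 4.
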